### 5.3.3 Safety Analysis

Safety outcomes will be assessed in the Safety population (i.e., any participant who was vaccinated) by study cohort for full and lower doses. All adverse events, serious adverse events, or deaths will be summarised as n (%) by study cohort and by study arm, where n is the number of participants that experienced any event post-vaccination and as a percentage of the total safety population within the study arm. All events (AEs, SAEs, and deaths) will also be presented by MedDRA coding (both System Organ Class and Preferred Term), relatedness to study vaccine, and outcome.

The proportion of participants in each study arm reporting any local reaction will be compared using the Chi-squared test and the difference in proportions with 95% confidence intervals will be presented. This will be repeated for systemic reactions.

All SAEs will be described in detail for each participant. The proportion of participants in each study arm reporting at least one SAE will be compared using Chi-squared test or Fisher's exact test, depending on the distributional assumptions.

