## **8. TRIAL DESIGN**

### **8.1. Overall Study Design and Plan Description**

This will be a parallel group, randomized, controlled, blinded, non-inferiority trial of four different doses of YF vaccine. The study will be conducted at the KEMRI CGMRC in Kilifi, Kenya and at Epicentre in Mbarara, Uganda. Both these sites are already working together in an ongoing study (Clinicaltrials.gov number: NCT02991495).

Adult participants (n=480) will be randomized for vaccination with full standard dose or with 1000, 500 or 250 IU (i.e. 4 arms) with a 1:1:1:1 allocation ratio. Results for the safety and primary outcome of the adult study will then be reviewed by the DSMB, and the lowest non-inferior dose in the adult study selected for assessment in children aged 9 to 12 months (n=420) in comparison to full standard dose (i.e. 2 arms), when co-administered with the EPI Measles vaccine, with a 1:1 allocation ratio. The determination of the non-inferior dose to use in children will be made by the sponsor in discussion with the study DSMB, vaccine manufacturer and relevant stakeholders, and the final decision communicated to the various regulatory authorities as a notification (i.e. SERU, OXTREC and PPB for the Kilifi site, MUST-REC, UNCST and NDA for the Mbarara site).

Adult vaccinees will be followed up for 2 years, and children for 1 year. There will be no gradual age de-escalation on the basis that there are few safety concerns with the full dose of YF vaccines, having been used in millions of children worldwide. The study procedures will be similar across both sites and these are summarized in Table 2.

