### 3.4 Selection of lowest non-inferior dose group for sub-study

Following the primary analysis time point, the DSMB will determine whether there is sufficient evidence of efficacy and safety to continue the trial in Cohort(B) and will offer a recommendation on which lowest non-inferior dose group to use in the sub-studies.

First, the DSMB shall assess non-inferiority at Day 28 of seroconversion rates (primary analysis), GMT, and GMFI for each dose groups in the adult PP and ITT populations. Any vaccine dose group (i.e.1000 IU, 500 IU, 250 IU) that is shown to be non-inferior in seroconversion and for which no concerns regarding significant variation are noted on secondary analysis will be considered for use in the sub-studies. If the lower doses are inferior to the full dose of all four vaccines, the sub-studies in populations (B) will not be conducted.

The primary endpoint will be assessed 28 days post-vaccination, but study visits will continue for up to two years after vaccination. Venous blood samples for YF titre quantification by PRNT will be collected at baseline, Viremia visit (2-7 days), 10 days (+/- 1 day), 28 days (+/- 3 days), 1 year (+/- 14 days) and 2 Years (+/- 28 days) after vaccination. PRNT for paired samples will be run at the same time to assure comparability of measurements from samples at baseline, 10 days, 28 days, 365 days and 2 years post-vaccination. The quantification of antibodies will be done at the Institut Pasteur in Dakar, Senegal. PRNT is considered the most sensitive and specific test for quantification of neutralizing antibodies and is the reference method for assessing immune response after vaccination.

*Table 1: Study activities timeline*

| Procedure                                     | Screening
Day -30* | Day 0            | Day 2, 3,
4, 5, 6, 7** | Day 10
(+/- 1 day) | Day 28
(+/- 3 days) | Day 365
(+/-14
days) | Day 730
(+/- 28
days) |
|-----------------------------------------------|-----------------------|------------------|---------------------------|-----------------------|------------------------|----------------------------|-----------------------------|
| Informed Consent                              | X                     |                  |                           |                       |                        |                            |                             |

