#### *Secondary Non-Inferiority Analysis*

Secondary analyses will include assessment of seroconversion in the ITT population as a whole, on the subset of the ITT population with baseline seropositivity to YF, and in the subset of the PP population with no reported history of flavivirus infection. Geometric mean PRNT50 titre (GMT) and GMT fold increase (GMFI) and corresponding 95% confidence intervals (CI) on day 0 and 28 will be calculated. Non-inferiority will be calculated by the difference in GMT and GMFI between the full dose and each lower dose group. Titres will be graphically represented by reverse cumulative distributions obtained by plotting, for each possible value of the titre (abscissa), the proportion of subjects with a titre greater than this value.

Lower vaccine doses may change the kinetics of antibody response. The assessment of seroconversion rates, GMT, and GMFI 10 days after vaccination in the ITT population will provide important information in the context of low dose vaccine usage in outbreak response. These three immunogenicity outcomes will also be assessed at 1 year and 2 years post-vaccination in the ITT population to confirm a lasting effect of full and low dose vaccination.

Relationships between seroconversion and vaccine immunogenicity (PRNT50 GMT and GMFI) will be related to frequencies of specific T and B cell subsets measured by flow cytometry, chemokine and cytokine levels in sera and neutralising antibody levels to other flaviviruses. Correlations between vaccine viraemia and immunogenicity will be assessed across the different vaccine dose strata. Comparisons of immune and viraemia kinetics will be made between the adult and children trial participants using non-parametric tests, whilst accounting for the administered vaccine dose.

Adverse events occurring during the study follow up period will be analyzed and compared between groups. This will be a descriptive analysis and will include all AEs up to 28 days post-vaccination, and SAEs that occurred any time during study follow-up.

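### SAEs are compared between arms by a significance test alone, with no risk difference, confidence interval or Day 28 window: a modest weakness in a supporting safety analysis

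*Supplement*

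**What the plan says.** SAP 5.3.3 treats two kinds of safety outcome differently. For local reactions, and again for systemic reactions, arms are compared by a chi-squared test and "the difference in proportions with 95% confidence intervals will be presented". For SAEs, the proportion in each arm "reporting at least one SAE will be compared using Chi-squared test or Fisher's exact test", and no difference, ratio or interval is named. The section does not say whether this is one four-arm test or a set of comparisons with the full dose.

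On timing, the safety paragraph under Secondary Non-Inferiority Analysis (SAP 5.3.2) covers AEs to Day 28 "and SAEs that occurred any time during study follow-up". Protocol 8.1 sets the length of that follow-up: "Adult vaccinees will be followed up for 2 years, and children for 1 year". SAEs are actively sought up to Day 28 and passively reported afterwards (protocol 12.1, SAP 4.2.1), although the visit schedule also marks AE/SAE assessment at Days 365 and 730. The planned AE tables stop at Day 28. SAE Tables 3.15 to 3.22 carry no time limit.

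On status, the same paragraph of SAP 5.3.2 states "This will be a descriptive analysis", protocol 13.2.3 agrees, and SAP 3.2 classes safety endpoints as supporting only.

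**The concern.** The more serious outcome gets the less informative output. A p-value on a handful of SAEs cannot show how large an excess the data still allow, whereas an interval can. The plan calls the analysis descriptive yet makes a hypothesis test its only stated between-arm comparison. A descriptive analysis calls for an estimate with its uncertainty.

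The open window adds to this. A vaccine effect on SAEs is expected early: protocol 12.8 ties expedited reporting of vaccine-linked SAEs to 28 days, and protocol 5.4 places viscerotropic disease within 10 days. Pooling those weeks with a year or two of background admissions can hide an early excess. At stake is what a reader may conclude about the comparative safety of the lower doses when few SAEs occur.

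**Working it through.** **Arm sizes.** The plan states no SAE rate and no power for SAEs, so only the sizes can be reproduced. From n = (1.960 + 1.282)² × 2p(1 − p)/0.10²:

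- Adults, p = 0.95: 10.51 × 0.095/0.01 = 99.8, so 100; × 1.2 = 120 per arm, as stated.
- Children, p = 0.90: 10.51 × 0.18/0.01 = 189.2, so 190; × 1.1 = 209, stated as 210 per arm.

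**Power of the SAE test.** Exact power is the sum over all counts (a, b) of Bin(a; n, p₀) × Bin(b; n, p₁), taken where the two-sided test gives p ≤ 0.05. The 5% level is from SAP 5.3. The SAE risks are assumptions.

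| Per arm | Assumed SAE risk, full vs lower dose | Fisher | Uncorrected chi-squared |
|---|---|---|---|
| 120 | 1% vs 2% | 1% | 7% |
| 120 | 1% vs 3% | 6% | 18% |
| 120 | 1% vs 5% | 28% | 44% |
| 120 | 2% vs 4% | 6% | 13% |
| 120 | 5% vs 10% | 22% | 33% |
| 120 | 5% vs 15% | 67% | 76% |
| 210 | 1% vs 2% | 5% | 12% |
| 210 | 2% vs 4% | 14% | 22% |
| 210 | 5% vs 10% | 43% | 49% |
| 210 | 5% vs 15% | 92% | 94% |

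With no SAE in one adult arm, significance needs at least 6 in the other by Fisher's test, or 4 by chi-squared. A single four-arm chi-squared test, with all three lower doses at 4% against 2%, has about 10% power (simulation).

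**What an interval would add.** Take 2/120 against 6/120. Fisher's p is 0.28. The Wilson 95% limits are (x + z²/2 ± z√(x(n − x)/n + z²/4))/(n + z²), which give 0.46% to 5.87% and 2.31% to 10.48%. The difference is 5.00 − 1.67 = 3.33 points, and Newcombe's limits are:

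- lower: 3.33 − √((5.00 − 2.31)² + (5.87 − 1.67)²) = 3.33 − 4.99 = −1.7
- upper: 3.33 + √((10.48 − 5.00)² + (1.67 − 0.46)²) = 3.33 + 5.61 = +8.9

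By the same method, 0 against 0 in 120 gives −3.1 to +3.1 points. For children, 4/210 against 8/210 gives p = 0.38 and −1.5 to +5.6 points.

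**Effect of the window (Fisher).**

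- Adults: assume a 5% two-year background spread evenly, so 5% × 28/730 = 0.19% falls in 28 days. An early excess of 5 points has 53% power in a 28-day window and 22% over two years. An excess of 2 points has 4% and 5%, so the window does not help there.
- Children: an early excess of 4 points has 70% power in a 28-day window (0.5% vs 4.5%), but 30% (5% vs 9%) or 20% (10% vs 14%) over the year.

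**The case against.** The strongest reply is that little information is lost. SAP 5.3.3 also requires n (%) with SAEs by arm, coding, relatedness and outcome by arm, and a detailed description of every SAE, so anyone can compute a whole-follow-up difference from the published counts. The Day 28 AE tables by arm include serious events, since an AE is any untoward occurrence. Counting SAEs over the whole follow-up matches the stated objective. No interval can inform on an event at 1 in 100,000: the chance of even one case of viscerotropic disease among all 900 participants is 1 − (1 − 10⁻⁵)⁹⁰⁰ = 0.9%.

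Most of this stands and limits the size of the point. What remains is that the Day 28 AE tables do not isolate serious events. Grade 4 implies an SAE, but by the protocol's own grading text an event can be serious without being severe. Protocol 12.8 tabulates SAEs to Day 28 for each population, but states no comparison by arm.

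A reader might also infer that the DSMB must judge whether there is "sufficient evidence of efficacy and safety to continue the trial in Cohort(B" from a p-value diluted by two years of background events. The documents do not support that. SAP 3.4 does not tie the safety judgement to this test. SAP 5.1.1 places the review at the adult Day 28 analysis point. The DSMB also receives SAE summaries and each vaccine-linked SAE, and may ask for further safety data (protocol 12.8 and 18.8).

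**Conclusion.** The point holds as a modest weakness in a supporting safety analysis. The stated SAE comparison is a test without an estimate or interval, and without a Day 28 comparison by arm. At low assumed SAE rates its non-significance carries little information: about 6% power for 1% against 3% with 120 per arm, and p = 0.28 beside an interval reaching +8.9 points for 2 against 6 events.

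It would go too far to say that a non-significant result is near certain whatever the truth. That depends on rates the documents do not give. It fits a doubling from about 1% or less, but not a tripling from 5% (67% power in adults, 92% in children). Nor do the documents say that non-significance will be read as comparable safety. The primary result, sample size and dose-selection rule are unaffected.

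**What to change.** In SAP 5.3.3 and Table 3.15, report the SAE risk difference for each lower dose minus full dose, with a 95% score-type interval (Newcombe or Miettinen-Nurminen). Give it for SAEs with onset on Days 0–28 and for the whole follow-up, side by side. Keep the whole-follow-up analysis, because it matches the objective and retains late events. State that any p-value is descriptive and that non-significance is not evidence of comparable safety.

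Onset dates are already collected (SAP 4.2, protocol 12.5), so the cost is a few lines of wording and one or two table columns. The downside is wide intervals that look less reassuring than a non-significant p-value. They show the imprecision of these arm sizes but do not remove it.

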### 5.3.4 Statistical Software

The analysis will be performed using Stata. Other packages such as R or SAS may be used if deemed necessary.

## 6. Statistical Tables to be Generated

### 6.1 Demographic and Baseline

|           |                                                                       |
|-----------|-----------------------------------------------------------------------|
| Table 1.1 | Summary of Screening and Vaccination                                  |
| Table 1.2 | Summary of Subject by Study Arm, Randomized Subjects and study cohort |
| Table 1.3 | Summary of Premature Discontinuation by Study Arm, Study Cohort       |
| Table 1.4 | Summary of Protocol Deviations by Study Arm and Study Cohort.         |

|           |                                                                                    |
|-----------|------------------------------------------------------------------------------------|
| Table 1.5 | Summary of Demographics and Baseline Characteristics by Study Arm and Study Cohort |
|-----------|------------------------------------------------------------------------------------|

## 6.2 Immunogenicity Analysis

### Seroconversion

|            |                                                                                                                                                                             |
|------------|-----------------------------------------------------------------------------------------------------------------------------------------------------------------------------|
| Table 2.1  | Non-inferiority of seroconversion rate in each lower dose vs. full dose of YF vaccine at Day 28 (Primary outcome) in adult PP population                                    |
| Table 2.2  | Non-inferiority of seroconversion rate in in each lower dose vs. full dose of YF vaccine at Day 28 in adult ITT population                                                  |
| Table 2.3  | Non-inferiority of seroconversion rate in each lower vs. full dose of YF vaccine at Day 28 in adult ITT population with baseline sero-positivity to YF.                     |
| Table 2.4  | Non-inferiority of seroconversion rate in each of each lower vs. full dose of YF vaccine at Day 28 in adult PP population with no reported history of flavivirus infection. |
| Table 2.5  | Non-inferiority of seroconversion rate in each lower vs. full dose of YF vaccine at Day 10 in adult ITT population.                                                         |
| Table 2.6  | Non-inferiority of seroconversion rate with each lower vs. full dose of YF vaccine at Day 365 in adult ITT population.                                                      |
| Table 2.7  | Non-inferiority of seroconversion rate with each lower vs. full dose of YF vaccine at 2 years follow up in adult ITT population.                                            |
| Table 2.8  | Non-inferiority of seroconversion rate in each lower vs. full dose of YF vaccine at Day 28 in Children PP population                                                        |
| Table 2.9  | Non-inferiority of seroconversion rate in each lower vs. full dose of YF vaccine at Day 28 in Children ITT population                                                       |
| Table 2.10 | Non-inferiority of seroconversion rate in each lower vs. full dose of YF vaccine at Day 28 in Children ITT population with baseline seropositivity to YF                    |
| Table 2.11 | Non-inferiority of seroconversion rate in each lower vs. full dose of YF vaccine at Day 28 in Children PP population with no reported history of flavivirus infection       |
| Table 2.12 | Non-inferiority of seroconversion rate in each lower vs. full dose of YF vaccine at Day 10 in Children ITT population                                                       |
| Table 2.13 | Non-inferiority of seroconversion rate in each lower vs. full dose of YF vaccine at Day                                                                                     |

|  |                                |
|--|--------------------------------|
|  | 365 in Children ITT population |
|--|--------------------------------|

## Geometric Mean Titre

|            |                                                                                                                                                       |
|------------|-------------------------------------------------------------------------------------------------------------------------------------------------------|
| Table 2.14 | Non-inferiority of GMT in each lower vs full dose of YF vaccine at Day 28 in adult PP population                                                      |
| Table 2.15 | Non-inferiority of GMT in each lower vs. full dose of YF vaccine at Day 28 in adult ITT population                                                    |
| Table 2.16 | Non-inferiority of GMT in each lower vs. full dose of YF vaccine at Day 28 in adult ITT population with baseline seropositivity to YF                 |
| Table 2.17 | Non-inferiority of GMT in each lower vs. full dose of YF vaccine at Day 28 in adult PP population with no reported history of flavivirus infection    |
| Table 2.18 | Non-inferiority of GMT in each lower vs. full dose of YF vaccine at Day 10 in adult ITT population.                                                   |
| Table 2.19 | Non-inferiority of GMT in each lower dose vs. full dose of YF vaccine at Day 365 in adult ITT population                                              |
| Table 2.20 | Non-inferiority of GMT in each lower vs. full dose of YF vaccine at 2 years in adult ITT population                                                   |
| Table 2.21 | Non-inferiority of GMT in each lower vs. full dose of YF vaccine at Day 28 in Children PP population                                                  |
| Table 2.22 | Non-inferiority of GMT in each lower vs. full dose of YF vaccine at Day 28 in Children ITT population                                                 |
| Table 2.23 | Non-inferiority of GMT in each lower vs. full dose of YF vaccine at Day 28 in Children ITT population with baseline seropositivity to YF              |
| Table 2.24 | Non-inferiority of GMT in each lower vs. full dose of YF vaccine at Day 28 in Children PP population with no reported history of flavivirus infection |
| Table 2.25 | Non-inferiority of GMT in each lower vs. full dose of YF vaccine at Day 10 in Children ITT population                                                 |
| Table 2.26 | Non-inferiority of GMT in each lower vs. full dose of YF vaccine at Day 365 in Children ITT population                                                |

## Geometric Mean Fold Increase

|            |                                                                                                                                                        |
|------------|--------------------------------------------------------------------------------------------------------------------------------------------------------|
| Table 2.27 | Non-inferiority of GMFI in each lower vs. full dose of YF vaccine at Day 28 in adult PP population                                                     |
| Table 2.28 | Non-inferiority of GMFI in each lower vs. full dose of YF vaccine at Day 28 in adult ITT population                                                    |
| Table 2.29 | Non-inferiority of GMFI in each lower vs. full dose of YF vaccine at Day 28 in adult ITT population with baseline seropositivity to YF                 |
| Table 2.30 | Non-inferiority of GMFI in each lower vs. full dose of YF vaccine at Day 28 in adult PP population with no reported history of flavivirus infection    |
| Table 2.31 | Non-inferiority of GMFI in each lower vs. full dose of YF vaccine at Day 10 in adult ITT population                                                    |
| Table 2.32 | Non-inferiority of GMFI with fractional vs. full dose of YF vaccine at Day 365 in adult ITT population                                                 |
| Table 2.33 | Non-inferiority of GMFI with fractional vs. full dose of YF vaccine at Day 2 years in adult ITT population                                             |
| Table 2.34 | Non-inferiority of GMFI in each lower vs. full dose of YF vaccine at Day 28 in Children PP population                                                  |
| Table 2.35 | Non-inferiority of GMFI in each lower vs. full dose of YF vaccine at Day 28 in Children ITT population                                                 |
| Table 2.36 | Non-inferiority of GMFI in each lower vs. full dose of YF vaccine at Day 28 in Children ITT population with baseline seropositivity to YF              |
| Table 2.37 | Non-inferiority of GMFI in each lower vs. full dose of YF vaccine at Day 28 in Children PP population with no reported history of flavivirus infection |
| Table 2.38 | Non-inferiority of GMFI in each lower vs. full dose of YF vaccine at Day 10 in Children ITT population                                                 |
| Table 2.39 | Non-inferiority of GMFI in each lower vs. full dose of YF vaccine at Day 365 in Children ITT population                                                |

